## Abstract

**Background:**

Major depression is a common mental health problem in the general population, associated with a substantial impact on quality of life and societal costs. However, many depressed patients in primary care do not receive the care they need. Reason for this is that pharmacotherapy is only effective in severely depressed patients and psychological treatments in primary care are scarce and costly. A more feasible treatment in primary care might be computerised cognitive behavioural therapy. This can be a self-help computer program based on the principles of cognitive behavioural therapy. Although previous studies suggest that computerised cognitive behavioural therapy is effective, more research is necessary. Therefore, the objective of the current study is to evaluate the (cost-) effectiveness of online computerised cognitive behavioural therapy for depression in primary care.

**Methods/Design:**

In a randomised trial we will compare (a) computerised cognitive behavioural therapy with (b) treatment as usual by a GP, and (c) computerised cognitive behavioural therapy in combination with usual GP care. Three hundred mild to moderately depressed patients (aged 18–65) will be recruited in the general population by means of a large-scale Internet-based screening (*N *= 200,000). Patients will be randomly allocated to one of the three treatment groups. Primary outcome measure of the clinical evaluation is the severity of depression. Other outcomes include psychological distress, social functioning, and dysfunctional beliefs. The economic evaluation will be performed from a societal perspective, in which all costs will be related to clinical effectiveness and health-related quality of life. All outcome assessments will take place on the Internet at baseline, two, three, six, nine, and twelve months. Costs are measured on a monthly basis. A time horizon of one year will be used without long-term extrapolation of either costs or quality of life.

**Discussion:**

Although computerised cognitive behavioural therapy is a promising treatment for depression in primary care, more research is needed. The effectiveness of online computerised cognitive behavioural therapy without support remains to be evaluated as well as the effects of computerised cognitive behavioural therapy in combination with usual GP care. Economic evaluation is also needed. Methodological strengths and weaknesses are discussed.

**Trial registration:**

The study has been registered at the Netherlands Trial Register, part of the Dutch Cochrane Centre (ISRCTN47481236).

## Background

Major depression is a common mental health problem in the general population [1] and it is reported to be the second most common and costly mental health problem in general practice [2]. Depression is associated with substantial decreases in quality of life through its impact on physical, social and emotional functioning, and well-being [3,4]. By 2020, depression is estimated to be the second leading contributor to the global burden of disease [5]. Cost-of-illness studies reveal that the economic burden of depression is considerable [6-8].

### Difficulties in the treatment of depression in primary care

The general practitioner (GP) is the major health care provider involved in the primary care treatment of depression. In the Dutch health care system the GP is seen as a gatekeeper, and as a result patients view their GP as a key figure in the detection and treatment of depression [9]. Despite this, many depressed patients remain undetected [10-12]. Even when the depressive complaints are being recognised, many patients in primary care do not receive the care they need. There are several reasons for this. First, time for the management of psychosocial problems is lacking [13]. Second, pharmacotherapy is only effective in extremely depressed patients [14], and many patients refuse medication or comply poorly [15]. Third, effective non-pharmacological treatment options, such as psychotherapy, in primary care are scarce or not feasible [16]. Consequently, only a limited group of depressed patients in primary care receives effective treatment.

### Computerised cognitive behavioural therapy in primary care

Cognitive behavioural therapy (CBT) is one the most widely researched forms of psychotherapy. Cognitive behavioural therapy (CBT) has proven to be as effective as pharmacotherapy in the acute phase of mild to severe depression, and seems even more effective in the prevention of recurrence and relapse [17-19]. Despite its effectiveness, face-to-face CBT in primary care has some major limitations. There are not enough well trained therapists, it is costly, there are waiting lists, and patients may feel reluctant to enter psychotherapy. An alternative treatment in primary care might be computerised cognitive behavioural therapy (CCBT): a computer program based on the principles of CBT. The level of therapist support can vary considerably in CCBT. It can be offered as a self-help intervention without or with only minimal support. Previously, written self-help based on CBT seemed a promising treatment for depression [20]. In a primary care setting, positive outcomes were found regarding the (cost-) effectiveness of written self-help with minimal contact in subthreshold depression relative to care as usual provided by the GP [21,22].

CCBT for primary care seems promising; it provides an acceptable alternative to pharmacotherapy, it can save clinicians' time, and the costs are low compared with face-to-face CBT. Furthermore, CCBT has a high accessibility, the number of referrals to secondary care by a GP can be reduced, and waiting lists for traditional CBT can become shorter [23,24]. Next to that, CCBT may fit very well in a stepped care program, and may function as a first step in the treatment of depression [25]. In a recent systematic review [23], it was concluded that CCBT is a feasible, effective and acceptable treatment for depression. However, most research on the efficacy of CCBT has been conducted in the general population or within clinical or specialist settings. To our knowledge, only one study, so far, investigated the efficacy of CCBT for depression in primary care [26], and it was shown that CCBT (delivered on a personal computer in the general practice) is more effective than usual care by a GP in mild to moderate depression and anxiety. Furthermore, this intervention seemed promising regarding the cost-effectiveness compared with usual GP care. CCBT was both more effective and more costly compared with usual GP care. When willing to pay for an additional unit of effect, CCBT could be very cost-effective. If a value of £40 is placed on a unit reduction on the Beck Depression Inventory, the probability of CCBT being cost-effective is in excess of 80%. At a value of £5000 for 1 quality-adjusted life-year (QALY), the study showed that there is an 85% chance of CCBT being more cost-effective, and at a value of £15000 per QALY it exceeds a 99% chance of being cost-effective [27]. Nevertheless, more research is necessary; so far only this one study has conducted an economic evaluation of CCBT, and the effects of CCBT in combination with usual care by a GP are still unknown. In addition the efficacy of CCBT via the Internet in primary care remains to be evaluated. The Internet can offer further advantages in comparison to CCBT on a stand-alone computer; it is easily accessible and it can be used at home, anonymously, and it is available 24/7.

### Current study

In the present study we aim to evaluate the (cost-) effectiveness of online CCBT for mild to moderate depression in primary care. In a randomised trial we will compare (a) CCBT with (b) treatment as usual (TAU) by a GP, and (c) CCBT in combination with TAU. In a recent Dutch study of Spek et al. (2007), the same CCBT program has shown to be equally effective as group CBT in people over 50 years old with subthreshold depression [28]. Based on the results from a recent systematic review [23] we hypothesise that CCBT will be more effective than TAU by a GP. Furthermore, we hypothesise that CCBT in combination with TAU will be more effective than CCBT alone by increasing treatment adherence. Although some studies have shown that for mild depression a combination of pharmacotherapy and psychotherapy does not appear more effective than psychotherapy alone [29], other studies suggested that patients receiving combined treatments were more likely to stay in treatment and comply to the treatment protocol [30].

Regarding the economic evaluation we hypothesise the following. The self-help intervention CCBT alone implies costs of time spent by the patient on the treatment and costs of the development of the program, while the TAU treatment requires costs related to a GP consult and/or medication. We hypothesise that from a societal perspective, these costs of the intervention CCBT are comparable to the costs of the intervention TAU. However, as a consequence of our hypothesis that CCBT is more effective than TAU, we expect that CCBT will be more preventive in health care use and productivity loss during the follow-up period, and thus result in lower costs compared with TAU by a GP. As a consequence of the expected increase of effectiveness (in terms of depression and quality of life) and decrease of costs, we hypothesise that CCBT is more cost-effective than TAU by a GP. Hypotheses about the intervention CCBT in combination with TAU are that it is both more costly and more effective compared with stand alone CCBT or TAU.

## Methods

### Design

We will conduct a randomised controlled trial. Patients will be randomly allocated to one of the three following conditions: (a) CCBT, (b) TAU by a GP, and (c) a combination of CCBT and TAU by a GP. The design of the study and the anticipated flow of the participants are graphically shown in Figure 1. The Medical and Ethical Committee of Maastricht University approved the study protocol. The study is registered at the Netherlands Trial Register, part of the Dutch Cochrane Centre (ISRCTN47481236).

**Figure 1 F1:**
[figure not shown]
Flow of the participants.

### Study population

The patient population we aim to investigate consists of 300 mild to moderately depressed adults. Patients are eligible to participate if they meet the following criteria: age 18 to 65 years; access to the Internet at home; at least mild to moderate depressive complaints (BDI-II score > 16), although a DSM-III-R diagnosis of major depression was not required; duration of depressive complaints 3 months or more; no current psychological treatment for depression; no continuous antidepressant treatment for 3 months or more prior to entry; fluent in Dutch language; no alcohol and/or drug dependence; and no severe psychiatric co-morbidity (e.g. psychotic disorders).

### Sample size

Power calculations are based on elementary head-to-head comparisons of CCBT versus usual care and CCBT versus the combined treatment (t-test). A clinically relevant treatment effect is derived from the only study of CCBT in primary care [26]. For a mean difference in change scores of 5 (SD 5.25) on the BDI-II, a sample size of 84 participants per group is needed (power 90%, alpha 0.05). Adjusting for potential study withdrawal (20%), we estimate that 100 participants per group are needed.

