### Randomisation and procedure

Randomisation will take place after informed consent is obtained. An independent statistician will develop the randomization code. Block randomization will be used to ascertain that each intervention consists of equally large groups. The randomization code will be given to an independent IT-specialist who will develop a computer program to carry out the group allocation. On entry into the trial the computer program provides the next available number. The randomization code will not be revealed until participant inclusion is complete. In view of the nature of the treatments, blinding of the participants and researchers is not possible.

Baseline assessment will take place at the research centre before randomization. The questionnaires will be administered on a computer. All follow-up assessments will take place at home via the Internet at two, three, six, nine and twelve months after inclusion. Preceding an upcoming assessment point, participants will receive an email alert. If a participant fails to complete the assessment within one week, an email-reminder will be sent. When the participant still fails to fill out the questionnaires, a phone call will be made.

Individuals will not be paid for participation, but will receive a small fee for Internet use.

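### The stated 84 per group does not follow from a difference of 5 with SD 5.25, which gives about 25; the 20% withdrawal allowance is also slightly short

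*Protocol article*

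**What the plan says.** The Sample size section of the protocol article names the test and the contrasts: "Power calculations are based on elementary head-to-head comparisons of CCBT versus usual care and CCBT versus the combined treatment (t-test"). It takes its treatment effect from the one earlier trial of computerised CBT (CCBT) in primary care, and continues: "For a mean difference in change scores of 5 (SD 5.25) on the BDI-II, a sample size of 84 participants per group is needed", with the error rates given as "power 90%, alpha 0.05". The allowance for loss comes next: "Adjusting for potential study withdrawal (20%), we estimate that 100 participants per group are needed". The Study population section gives a total of 300, and the Randomisation and procedure section confirms equal allocation: "Block randomization will be used to ascertain that each intervention consists of equally large groups". The article gives no other SD, no design factor and no multiplicity adjustment for the sample size, and it does not say whether alpha is one- or two-sided.

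**The concern.** All the ingredients of a two-group calculation are printed, so the result can be checked directly. A difference almost as large as its SD is a large effect and needs a few dozen participants per group, not 84. The allowance for withdrawal also looks as if 84 had been multiplied by 1.2 rather than divided by 0.8.

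This paragraph is the only justification given for 300 participants, and the possible explanations point in opposite directions. If the printed difference and SD are right, the trial is much larger than its stated target requires. If the SD is really near 10, the printed SD is wrong and the 90% claim is narrowly missed after the planned withdrawal. As written, a reader cannot tell which effect the trial was sized to detect.

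**Working it through.** **Inputs, all from the Sample size section:** difference in change scores 5; SD 5.25; power 90%; alpha 0.05; t-test between two equal groups; stated size 84 per group; withdrawal 20%; enrolment 100 per group. Two-sided testing is my assumption; one-sided is tried below.

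**Step 1. Try to reproduce 84.**
- Standardised effect: d = 5 / 5.25 = 0.952.
- Normal approximation: n = 2 × (1.960 + 1.282)² / d² = 2 × 10.51 / 0.907 = 23.2, so 24 per group.
- Exact (noncentral) t-test: 24.2, so 25 per group.
- Stated figure over computed figure: 84 / 25 = 3.4. The stated figure is not reproduced.

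**Step 2. Try other readings.** All use 90% power and the exact t-test unless noted.

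| Reading | n per group |
|---|---|
| One-sided alpha 0.05 | 20 |
| Two-sided alpha 0.025 (two comparisons) | 29 |
| Two-sided alpha 0.0167 (three pairs) | 32 |
| Two-sided alpha 0.01, 95% power | 41 |
| SD multiplied by √2 | 48 |
| SD doubled | 94 |
| Three-group ANOVA, several patterns of means | about 20 to 29 |

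None gives 84 per group. The one numerical match is 3 × 28 = 84 as a total over three groups, using alpha 0.025 and the normal approximation. That contradicts the printed alpha of 0.05 and the wording "a sample size of 84 participants per group is needed", so it remains conjecture.

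**Step 3. What 84 per group does correspond to** (two-sided alpha 0.05, 90% power).
- Normal approximation: d = (1.960 + 1.282) × √(2/84) = 0.500. Exact t-test: d = 0.503.
- With the difference held at 5: SD = 5 / 0.503 = 9.94.
- With the SD held at 5.25: difference = 0.503 × 5.25 = 2.64 points.
- Conversely, d = 0.50 gives n = 2 × 10.51 / 0.25 = 84.06 by the normal approximation and 85.03 by the exact t-test.
- With the printed difference and SD, power at 84 per group is above 99.99%.

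**Step 4. Withdrawal.**
- Needed to keep 84: 84 / (1 − 0.20) = 105 per group, or 315 in total.
- Left from 100: 100 × 0.80 = 80.
- 84 × 1.2 = 100.8, close to the stated 100. The article does not say how 100 was obtained.
- Enrolling 100 keeps 84 only if withdrawal is 1 − 84/100 = 16%.

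**Step 5. Effect of having 80 rather than 84 per group** (exact t-test, two-sided alpha 0.05).

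| Basis | Power at 84 | Power at 80 |
|---|---|---|
| d = 0.50 | 89.6% | 88.2% |
| d = 0.503 | 90.0% | 88.5% |
| d = 0.952 (as printed) | above 99.99% | above 99.99% |

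With 80 per group and 90% power the detectable effect is 0.516 SD. If SD 5.25 is confirmed, this is 0.516 × 5.25 = 2.7 points.

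**The case against.** The strongest reply is that nothing in the conduct of the trial depends on the discrepancy. On the printed inputs the trial is oversized, not underpowered, and the unfavourable case needs an SD near 10 that appears nowhere in the article and is only back-calculated from 84. This stands as a limit on the consequence. A reader might infer that the trial is underpowered, and the document does not support that. It does not rescue the paragraph, whose printed numbers cannot all be right.

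On withdrawal, the loss is about 1.5 percentage points of power, and only on the basis of an effect near 0.50. The Clinical analyses section also plans intention-to-treat analysis, multi-level models if necessary, and imputation for loss to follow-up once more than 15% of data are missing, so those who withdraw need not all drop out of the analysis. This is fair, and it makes the step secondary. Even so, an allowance for 20% loss that leaves 80 does not deliver the 84 it was meant to protect.

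A reader might also infer that applying the same 5 points to CCBT versus the combined treatment is an error, since the Background describes the source trial as comparing CCBT with usual GP care. The article presents 5 points as a clinically relevant target, and a common target may be set for both contrasts. A separate figure would be a preference and is not requested here.

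Finally, one might fear that a null result will be read against the wrong detectable difference. Nothing in the Analyses section says that results will be judged against the planning difference, so this is not claimed.

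**Conclusion.** The sample size statement is wrong as written. Its stated inputs require about 25 per group and it reports 84, a gap of 3.4-fold that no standard variant tried here closes. Two-sided testing is assumed, but one-sided testing moves the answer further from 84. At least one of the difference, the SD and the sample size is misstated, and the document does not show which. It would go too far to conclude that the true SD is about 10: that value is merely what 84 would imply for a 5-point difference.

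The withdrawal step is a separate, minor error: 105 per group would be needed to retain 84, and 100 retains 80. Its cost is about 88% instead of 90% power if the effect implied by 84 is the true basis, and nothing of practical size if SD 5.25 is correct.

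**What to change.** Go back to the original calculation and to the source of the treatment effect, check the difference, the SD and the sample size, and correct whichever is wrong. The SD should not simply be reset to the value that makes 84 come out.

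Then state that 100 enrolled per group leaves 80 evaluable at 20% withdrawal, and give the power at that number for the confirmed difference and SD, or the detectable difference at 90% power: about 0.52 SD, which is about 2.7 points if SD 5.25 is confirmed. State also whether alpha is two-sided.

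The cost is a look at the original calculation and the rewording of one paragraph. The restated power may be slightly below 90%. No extra enrolment is required, and the allocation, outcome and analysis are unchanged.

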### Recruitment

Participants will be recruited in the general population by means of a large-scale Internet-based screening in the South of the Netherlands. A random selection of individuals (*N *= 200,000) will be sent an invitation letter to complete a screening questionnaire (i.e. BDI for primary care) via the Internet. The letters will be sent in weekly badges. Six municipalities cooperate by issuing names and addresses of their residents on a weekly base. The letters will contain information on the study protocol as well as log in codes for the questionnaires on the Internet. Participants who score above the cut-off score of four on the BDI for primary care [31] will be invited to visit the research centre for an interview where final eligibility will be assessed based on the in- and exclusion criteria. After inclusion we will notify the patients' GP about his or her participation in the study.

### Randomisation and procedure

Randomisation will take place after informed consent is obtained. An independent statistician will develop the randomization code. Block randomization will be used to ascertain that each intervention consists of equally large groups. The randomization code will be given to an independent IT-specialist who will develop a computer program to carry out the group allocation. On entry into the trial the computer program provides the next available number. The randomization code will not be revealed until participant inclusion is complete. In view of the nature of the treatments, blinding of the participants and researchers is not possible.

Baseline assessment will take place at the research centre before randomization. The questionnaires will be administered on a computer. All follow-up assessments will take place at home via the Internet at two, three, six, nine and twelve months after inclusion. Preceding an upcoming assessment point, participants will receive an email alert. If a participant fails to complete the assessment within one week, an email-reminder will be sent. When the participant still fails to fill out the questionnaires, a phone call will be made.

Individuals will not be paid for participation, but will receive a small fee for Internet use.

### Interventions

The CCBT program (named "colour-your-life") is an online, multimedia, interactive, self-help computer program for depression, and was developed by Riper and Kramer (2004) [32] of the Trimbos-institute (the Netherlands Institute of Mental Health and Addiction). The program is based on the principles of CBT and on the Dutch version of the 'coping with depression course' of Lewinsohn [33,34]. The program consists of eight weekly 30-minute sessions and a ninth booster session, although the duration of sessions can vary among users. At the end of each session homework-assignments are given, such as keeping a 'mood diary'. Patients allocated to the intervention CCBT or the combination CCBT and TAU will be given log in codes by the researchers at inclusion and they will access the program at home. No professional assistance will be offered. The program was originally developed for people over 50-years old [28] and is adapted for an adult population (18 to 65 years) for the current study. GP's of patients allocated to CCBT only will be informed about the participation and treatment allocation of their patient.

In the TAU and CCBT&TAU group, participants will be advised to contact their own GP. GPs of patients in the TAU and the CCBT&TAU group will be sent a letter, informing them about their patients' study participation, and advising them to follow the depression guideline as described by the Dutch College of General Practitioners [35]. This guideline states that treatment should formally consist of four to five biweekly consultations over the course of nine weeks in combination with antidepressant treatment if indicated. In case of suicidal risk, social dysfunction, symptom deterioration or non-improvement in six to twelve weeks time, referral to specialist mental health care settings is recommended. In practice however, usual care is whatever the GP prescribes.

An integrity check will be performed to assess treatment quality and protocol compliance using computer records of the CCBT program and questionnaires assessing use of GP and other health care (i.e. health care use questionnaire).

